## Abstract

**Background:**

Although the release of cardiac biomarkers after percutaneous (PCI) or surgical revascularization (CABG) is common, its prognostic significance is not known. Questions remain about the mechanisms and degree of correlation between the release, the volume of myocardial tissue loss, and the long-term significance. Delayed-enhancement of cardiac magnetic resonance (CMR) consistently quantifies areas of irreversible myocardial injury. To investigate the quantitative relationship between irreversible injury and cardiac biomarkers, we will evaluate the extent of irreversible injury in patients undergoing PCI and CABG and relate it to postprocedural modifications in cardiac biomarkers and long-term prognosis.

**Methods/Design:**

The study will include 150 patients with multivessel coronary artery disease (CAD) with left ventricle ejection fraction (LVEF) and a formal indication for CABG; 50 patients will undergo CABG with cardiopulmonary bypass (CPB); 50 patients with the same arterial and ventricular condition indicated for myocardial revascularization will undergo CABG without CPB; and another 50 patients with CAD and preserved ventricular function will undergo PCI using stents. All patients will undergo CMR before and after surgery or PCI. We will also evaluate the release of cardiac markers of necrosis immediately before and after each procedure. Primary outcome considered is overall death in a 5-year follow-up. Secondary outcomes are levels of CK-MB isoenzyme and I-Troponin in association with presence of myocardial fibrosis and systolic left ventricle dysfunction assessed by CMR.

**Discussion:**

The MASS-V Trial aims to establish reliable values for parameters of enzyme markers of myocardial necrosis in the absence of manifest myocardial infarction after mechanical interventions. The establishments of these indices have diagnostic value and clinical prognosis and therefore require relevant and different therapeutic measures. In daily practice, the inappropriate use of these necrosis markers has led to misdiagnosis and therefore wrong treatment. The appearance of a more sensitive tool such as CMR provides an unprecedented diagnostic accuracy of myocardial damage when correlated with necrosis enzyme markers. We aim to correlate laboratory data with imaging, thereby establishing more refined data on the presence or absence of irreversible myocardial injury after the procedure, either percutaneous or surgical, and this, with or without the use of cardiopulmonary bypass.

## Background

The release of creatine phosphokinase enzymes (CPK), CK-MB isoenzyme (CK-MB), cardiac troponin, or both, in the absence of ECG waves indicating necrosis during percutaneous or surgical procedures has occurred in 10 to 35 % of cardiac patients. These indices are considered diagnostic for acute myocardial infarction (AMI) [1,2]. Such results are important, because they are similar to those found during spontaneous cardiac events in the population of patients with coronary artery disease (CAD) [3]. The release of enzyme markers of myocardial cells allows the diagnosis of AMI, when the levels of CK-MB or troponin are elevated up to 3 times above the established standard for percutaneous interventions (PCI) and up to 5 times for surgical revascularization (CABG) even in the absence of electrocardiographic changes or clinical symptoms [4,5]. On the other hand, these indices, considered indicative of AMI, have prognostic value according to the severity of the patient and the procedure performed. In this scenario, the prognosis for this event can be associated with the degree of elevation of biomarkers released and with the type of intervention applied. Also included in the prognosis of the condition are the number of arteries involved, the degree of arterial and ventricular impairment, and the type of intervention performed.

However, both invasive and noninvasive investigations during the period after the intervention have limitations related to the poor the sensitivity and specificity of the ECG and biomarkers. Although cardiac-specific biomarkers potentially have the greatest role in simple detection of myocyte necrosis, their independent utility in this setting remains inaccurate.

To increase the diagnosis, the accuracy of delayed enhancement CMR imaging (DE-CMR) can quantify reversible and irreversible myocyte necrosis.

In fact in recent studies, Pegg et al. [6] reported increased cardiomyocyte necrosis associated with the hybrid technique of on-pump beating-heart CABG both detected by DE-CMR and biomarkers. In this study, the authors had as an end point the effectiveness of biomarkers troponin I (TnI) and creatine kinase-MB isoform (CK-MB) and compared these with CMR to diagnose AMI.

Moreover, these authors evaluated the efficacy of cardiac enzymes for determination of cardiomyocyte necrosis after CABG and compared this with the efficacy of CMR [7].

In the MASS-V study, we will prospectively examine the incidence and extent of new DE-CMR-defined irreversible injury in patients undergoing PCI or CABG and correlate it with postprocedural changes in TnI and CK-MB. Our hypothesis is that the releasing of biomarkers does not necessarily leads to myocardial fibrosis or left ventricular dysfunction; and the cut-off levels to define periprocedural AMI would be different from the ones established in current guidelines.

## Methods/Design

The MASS-V Trial is an institutional project that the Heart Institute (InCor), Hospital das Clinicas, University of São Paulo designed to prospectively investigate 150 patients with multivessel coronary artery disease (CAD) with normal left ventricle ejection fraction (LVEF) and with a formal indication for CABG or PCI. Fifty patients will be operated on with cardiopulmonary bypass (CPB) and another 50 patients with the same arterial and ventricular conditions and also with a proper indication for myocardial revascularization will be operated on without the help of the CPB circuit. Another 50 patients with CAD and preserved ventricular function with a formal indication for percutaneous coronary intervention (PCI) with the use of intracoronary "stents” will be analyzed.

The inclusion criteria will determine which patients are eligible for which of the three procedures. Anginal symptoms must be stable and the LVEF preserved. The main steps of the procedures are shown in Figure 1. Exclusion criteria include the following: recent myocardial infarction (≤6 months); signs of manifest or suspected infections or rheumatologic disease activity; chronic renal failure (creatinine level >2.0 mg/dL); recent (≤ 6 months) pulmonary embolism or venous thromboembolism; not signing the consent form; contraindication for the use of glycoprotein IIb/IIIa inhibitors or CMR examination, for example, a person with a pacemaker or severe claustrophobia.

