### Statistical analysis

Values will be expressed as mean (±SD) or median (interquartile range) as appropriate. The paired-sample *t* test and the unpaired-sample *t* test will be used to compare means within the study group or between subgroups. *χ*^2^ statistics with Fisher’s exact test will be used for comparison of discrete variables. Continuous variables that were not distributed normally will be compared with the Mann–Whitney *U* test, and correlation between such variables will be made with the Spearman rank test. Binary logistic regression will be performed to determine which clinical and angiographic parameters predict the likelihood of myocardial hyperenhancement. Multivariate logistical regression will be used to assess the relative contribution of various clinical and angiographic variables to the presence of new hyperenhancement after PCI or CABG. A probability value of <0.05 is considered statistically significant.

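### PCI versus CABG follows formal indication, the article describes the PCI population in conflicting ways, and the listed two-group tests and correlation neither adjust for baseline nor separate the procedures

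*Protocol article*

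**What the plan says.** **How patients enter a group.** Methods/Design states: "The inclusion criteria will determine which patients are eligible for which of the three procedures". The surgical groups are described thus: "Fifty patients will be operated on with cardiopulmonary bypass (CPB) and another 50 patients with the same arterial and ventricular conditions". The text does not say how surgical patients are divided between on-pump and off-pump. Figure 1, which covers enrolment, is not reproduced in the copy at hand.

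**Who the patients are.** The abstract describes all 150 as having "multivessel coronary artery disease (CAD) with left ventricle ejection fraction (LVEF) and a formal indication for CABG". Methods/Design describes the 150 as multivessel patients "with a formal indication for CABG or PCI", and then the PCI group separately: "Another 50 patients with CAD and preserved ventricular function with a formal indication for percutaneous coronary intervention (PCI").

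**What is analysed.** Under Statistical analysis, paired and unpaired t tests "will be used to compare means within the study group or between subgroups". Discrete variables get chi-square or Fisher tests. Non-normal variables get the Mann-Whitney test, with Spearman correlation. Logistic regression, including a multivariable model on clinical and angiographic variables, is planned for hyperenhancement after PCI or CABG. No adjusted analysis is named for marker levels, left ventricular function or death.

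**What is asked.** The Background aims to relate new irreversible injury on delayed-enhancement CMR to changes in TnI and CK-MB, and questions the guideline cut-offs for periprocedural infarction. Trial outcomes names 5-year death as primary, with marker levels in association with fibrosis and ventricular dysfunction as secondary.

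**The concern.** The Background itself says that prognosis depends on the number of diseased arteries, the degree of arterial and ventricular impairment, and the type of intervention. The first two are plausible reasons for sending a patient to surgery rather than PCI. A raw PCI versus CABG difference in a marker or in ventricular function would then partly show who was selected for which procedure.

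The stated aim is exposed too. The Discussion attributes marker release in surgery to handling of the heart, contact with the bypass circuit, cross-clamping and reperfusion, and injury in PCI to embolisation, side-branch occlusion, dissection and loss of collateral flow. The Background also quotes different diagnostic multiples for the two: 3 times the reference for PCI and 5 times for CABG. One correlation or cut-off taken over all patients could describe neither procedure.

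The conflicting descriptions make this harder to judge. If all patients share a CABG indication, PCI and CABG patients are closer to comparable. If each group has its own indication, they are not.

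**Working it through.** **1. Stated size.** 50 + 50 + 50 = 150, which reproduces. The article gives no effect size, SD or event rate, so there is no further figure to recompute.

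**2. Populations side by side.**

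| | Abstract | Methods/Design |
|---|---|---|
| Indication, all 150 | CABG | CABG or PCI |
| Indication, PCI group | CABG, as part of the 150 | PCI |
| Disease extent, all 150 | multivessel | multivessel |
| Disease extent, PCI group's own line | CAD | CAD |

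The indication rows cannot both stand. The last two rows leave it unclear whether PCI patients must have multivessel disease.

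**3. Which analyses adjust.** Only the multivariable logistic model for new hyperenhancement does, and procedure is not named among its variables. The t, Mann-Whitney, chi-square/Fisher and Spearman analyses carry no covariates or strata.

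**4. Illustration of confounding; every input except n is assumed.** Let a baseline factor differ between two groups by D (in SD) and correlate rho with the outcome, with no true procedure effect.

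- Bias = rho × D, in SD of the outcome.
- With 50 against 50, the standard error is sqrt(2/50) = 0.2, so the shift is z = bias/0.2.
- Rejection rate at two-sided 0.05 = Φ(z − 1.96) + Φ(−z − 1.96).

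| D | rho | Bias (SD) | z | Rejection rate |
|---|---|---|---|---|
| 0.25 | 0.3 | 0.075 | 0.375 | 6.6% |
| 0.5 | 0.3 | 0.15 | 0.75 | 11.7% |
| 0.5 | 0.4 | 0.20 | 1.0 | 17% |
| 0.5 | 0.5 | 0.25 | 1.25 | 24.0% |
| 0.75 | 0.5 | 0.375 | 1.875 | 46.6% |
| 1.0 | 0.5 | 0.50 | 2.5 | 70.5% |

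For a binary outcome, a factor present in 60% against 30% that doubles the risk gives a spurious risk ratio of (1 + 0.6)/(1 + 0.3) = 1.23.

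**5. Pooled correlation.** Spearman's coefficient is a correlation of ranks. The pooled covariance of ranks equals the average within-procedure covariance plus a between-procedure part. With 50 PCI and 100 CABG patients, that part is (50/150) × (100/150) = 0.22 times the product of the two mean rank differences (marker and injury). If both means differ, the pooled coefficient can be non-zero with no relation inside either procedure. If the differences have opposite signs, it can hide a real one. The article gives no figure for either difference, so neither direction nor size can be stated.

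**6. Room to adjust for death.** At an assumed 5-year mortality of 5% to 20%, 150 patients yield 150 × 0.05 = 7.5 to 150 × 0.20 = 30 deaths, enough for only a few coefficients.

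**The case against.** The strongest reply is that the article never says it will test PCI against CABG. Its tests are between unspecified subgroups, which could be patients with and without new hyperenhancement, and the stated hypothesis is about biomarkers and injury. This stands as far as it goes. A between-procedure comparison is an inference, though a reasonable one: the Figure 1 legend speaks of arms, and the abstract's Discussion frames the results by percutaneous or surgical procedure, with or without bypass. The conclusion is therefore conditional: if procedures are compared with these tests, the result is confounded. The pooled-correlation problem bears directly on the stated aim and does not depend on that inference.

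Three stronger readings are tempting and not supported.

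- A reader might infer that all three groups are formed by indication. The text shows this for PCI versus CABG only. The two surgical groups are said to share arterial and ventricular conditions, and silence on their split does not establish confounding.
- A reader might infer that death will be compared by an unadjusted test. The article names death as the primary outcome but states no test for it.
- A reader might infer that nothing is adjusted. A multivariable model is planned for new hyperenhancement, the injury outcome at the centre of the aim. It names no individual covariate, so the absence of procedure from its wording carries limited weight, and a fuller plan may supply it.

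It is also fair that no magnitude input comes from the documents.

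**Conclusion.** The point holds in limited form. The abstract and Methods contradict each other on the indication of the 50 PCI patients, and that is an error in the text whatever a fuller plan contains. PCI versus CABG is set by formal indication, so an unadjusted difference in TnI, CK-MB or left ventricular function would not isolate the effect of the procedure. A correlation or cut-off pooled over procedures would mix two relations.

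The size of any bias is unknown. The range of 6.6% to 70.5% shows only how strongly it depends on the assumed imbalance and correlation; it is not an estimate for this trial. For on-pump versus off-pump surgery, confounding is a possibility that the text neither shows nor excludes. The remedy is an inexpensive improvement to wording and analysis, and the aim of relating biomarkers to injury remains sound.

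**What to change.** 1. Reconcile the abstract with Methods/Design so that each group has one stated population: indication, disease extent and ventricular function.
2. State that PCI versus CABG is not randomised, and state how surgical patients are assigned to on-pump or off-pump.
3. Estimate the biomarker-injury relations and any cut-offs within procedure.
4. Include procedure in the planned model for new hyperenhancement.
5. Either report PCI versus CABG differences as descriptive, or test them with a model adjusting for the pre-procedure marker and for the baseline clinical, angiographic and CMR variables the study already collects. For death, keep adjustment to very few terms. The choice of covariates and of adjustment technique can be left to the analysis plan.

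The cost is protocol wording and analysis programming. Markers and CMR are already scheduled before each procedure, and Trial status says enrolment had not begun at submission. The price is somewhat less precise estimates, because within-procedure analyses use fewer patients and adjusted models spend degrees of freedom, and softer claims about PCI against CABG.

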**Figure 1 F1:**
[figure not shown]
**Algorithm of MASS V Trial. **Legend: Enrollment and follow-up procedures in the arms of MASS V trial.

All patients will undergo CMR before and after surgical or percutaneous interventions to determine the presence or absence of myocardial necrosis complications after the procedure.

In addition, we will be evaluating the release of cardiac necrosis markers immediately before and after each procedure. The measurement of necrosis markers in the series will be conducted 6, 12, 24, and 36 hours after the percutaneous intervention. For the surgical procedures, dosage series will expand from 48 to 72 hours.

### CMR protocol

The patients will be studied in a 1.5-T clinical MR scanner (Philips Achieva), and steady-state free-procession cine images will be acquired in 2 long-axis (2 and 4 chambers view) and 8 to 10 short-axis views of the left ventricle. A gadolinium-based contrast agent (Gadoterate meglumine Gd-DOTA, Guerbet SA, France) will then be injected intravenously (0.1 mmol per kilogram of body weight), and contrast-enhanced images will be acquired after a 5- to 10-minute delay with the use of an inversion-recovery segmented sequence. Contrast-enhanced images will be acquired in long- and short-axis planes identical to the cine images. Typical voxel size will be 1.6x2.1x8mm, with a reconstruction matrix of 528 and a reconstructed voxel size of 0.6 mm. The method for acquiring and analyzing CMR is standardized in our service and is reproduced according to conventional techniques [2,8].

### Delayed enhancement

Delayed enhancement of cardiac magnetic resonance will be performed with a phase-sensitive inversion recovery (PSIR) sequence (repetition time 6.1, echo time 3.0 ms, voxel size 1.6x2.1x8mm, flip angle 25^o^) following a 5-min time delay after the administration of 0.1 mmol/kg contrast agent (Gadoterate meglumine Gd-DOTA, Guerbet SA, France). Images will be acquired in two long-axis planes and in a short-axis stack covering the entire left ventricle. The inversion time will be meticulously adjusted throughout the acquisition to obtain optimal nulling of remote normal myocardium. The slice thickness at the apex will be reduced to 5 mm to avoid a partial volume effect [7].

### CMR postprocessing and data analysis

All areas of late gadolinium-DTPA hyperenhancement will be quantified with a computer-assisted planimetry program - CMR42 v. (Circle Cardiovascular Imaging, Calgary, Canada) and interpreted by two experienced observers blinded to the interventional technique and biochemical data. When measurements are different, a third observer will perform a review and a consensus will be obtained.

Hyperenhanced pixels are defined as those with image intensities >2 SDs above the mean of image intensities in a remote myocardial region in the same image. Furthermore, we prospectively identified the site of any new hyperenhancement in relation to the implanted stent. Areas of new hyperenhancement that occur in the same short-axis image as the stent will be classified as adjacent to stent injury, whereas new hyperenhancement that occurs in the myocardium distal to the stent is deemed downstream injury.

Just as with a percutaneous intervention, hyperenhanced pixels will be defined as image intensities greater than two standard deviations above the mean intensities in a remote myocardial region in the same image. Preintervention and postintervention scans will be read side by side in both surgical techniques, with and without extracorporeal circulation.

### Biochemistry

Blood samples will be collected from each patient for measurement of troponin I (TnI) and CK-MB mass immediately before PCI and 6, 12, 24, and 36 hours after the procedure. For patients undergoing coronary artery bypass surgery, on-pump or off-pump, these cardiac markers will be measured immediately before surgery and 6, 12, 24, 36, 48, and 72 hours after surgery.

The surgeon and clinical team will be blinded to the CK-MB or TnI data.

All the samples will be centrifuged at 3000 rpm for 20 minutes and analyzed within 2 hours after specimen collection. TnI and CK-MB analysis will be performed in an immunoassay analyzer (ADVIA Centaur, Siemens Health Care Diagnostics, Tarrytown, NY). According to the manufacturer, the lower limit of detection of TnI using a high-sensitivity kit, the Ultra kit, is 0.006 ng/mL, and the 99th percentile and MI reference limits are respectively 0.04 and 0.76 ng/mL. The assay precision, represented by the percentage coefficient of variation (%CV) is ≤ 10 % at 0.03 ng/mL.

The detection limit of the CK-MB mass kit is 0.18 ng/mL, and the cut off values at the 99th percentile, established by our laboratory, are 3.8 ng/mL for women and 4.4 ng/mL for men. The CVs for CK-MB mass, as specified by the manufacturer, are 3.91 % at 3.55 ng/mL and 3.61 % at 80.16 ng/Ml.

### Statistical analysis

Values will be expressed as mean (±SD) or median (interquartile range) as appropriate. The paired-sample *t* test and the unpaired-sample *t* test will be used to compare means within the study group or between subgroups. *χ*^2^ statistics with Fisher’s exact test will be used for comparison of discrete variables. Continuous variables that were not distributed normally will be compared with the Mann–Whitney *U* test, and correlation between such variables will be made with the Spearman rank test. Binary logistic regression will be performed to determine which clinical and angiographic parameters predict the likelihood of myocardial hyperenhancement. Multivariate logistical regression will be used to assess the relative contribution of various clinical and angiographic variables to the presence of new hyperenhancement after PCI or CABG. A probability value of <0.05 is considered statistically significant.

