### Trial outcomes

Primary outcome considered is overall death in a 5-year follow-up. Secondary outcomes are levels of CK-MB isoenzyme and I-Troponin in association with presence of myocardial fibrosis and left ventricle ejection dysfunction assessed by CMR.

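### Between-group tests of continuous CMR measures such as LVEF name no adjustment for the pre-procedure scan planned for every patient, which costs precision and, in non-randomised groups, can carry baseline differences into the comparison

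*Protocol article*

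**What the plan says.** The Statistical analysis section of the protocol article fixes the method for continuous variables: paired and unpaired t tests, which "will be used to compare means within the study group or between subgroups". For the rest, "Continuous variables that were not distributed normally will be compared with the Mann–Whitney *U* test". The section does not say which variables are tested, what the subgroups are, or whether the unpaired test is applied to post-procedure values or to changes.

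The only covariate models named are logistic regressions for hyperenhancement. One of them assesses the "relative contribution of various clinical and angiographic variables to the presence of new hyperenhancement after PCI or CABG". No model is named for a continuous CMR measure.

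The baseline measurement is planned. Methods/Design, in the text after Figure 1, states: "All patients will undergo CMR before and after surgical or percutaneous interventions". The same section sets up three groups of 50 (on-pump CABG, off-pump CABG and PCI), lets the inclusion criteria decide which procedure a patient may have, requires preserved LVEF, and mentions no randomisation.

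Under Trial outcomes, CMR enters through the secondary outcome: biomarker levels "in association with presence of myocardial fibrosis and left ventricle ejection dysfunction assessed by CMR".

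**The concern.** Two scans of the same heart are usually correlated, so part of the spread in post-procedure LVEF is patient-to-patient difference already recorded at the first scan. An unpaired t test on post-procedure values leaves that spread in the error term. With 50 patients per group, the loss could decide whether a modest LVEF difference between procedures is seen.

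There is also a question of bias. Patients reach their procedure by eligibility, so mean LVEF may differ between groups before anything is done. A raw comparison of post-procedure values then mixes that starting difference with any effect of the procedure.

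Paired tests do not help here. A paired test describes change within one group and does not test whether two groups differ.

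**Working it through.** The article gives no effect size, SD, correlation or power, so there is no stated figure to reproduce.

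**Inputs from the article**
- 50 patients per group (Methods/Design).
- Significance level 0.05 (Statistical analysis). Sidedness is not stated; two-sided is assumed.
- CMR before and after in all patients (Methods/Design).

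**Assumptions**
- Pre–post correlation r from 0.3 to 0.8. Requiring preserved LVEF narrows the baseline range and may push r towards the lower end.
- Equal SD before and after, and similar baseline means across groups.
- For the illustration only: LVEF SD of 8 points and a true group difference of 3 points.

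**Step 1. Variance of the group difference, relative to a t test on post values (= 1)**
- t test on change: 2(1 − r)
- linear model with the baseline value as covariate (ANCOVA): 1 − r²
- ANCOVA relative to change: (1 − r²) / [2(1 − r)] = (1 + r)/2
- 50 per group with ANCOVA acts like 50/(1 − r²) per group on post values, or 50 × 2/(1 + r) per group on change.

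| r | change | ANCOVA | ANCOVA ÷ change | 50 acts like (vs post) | 50 acts like (vs change) |
|---|---|---|---|---|---|
| 0.3 | 1.40 | 0.91 | 0.65 | 55 | 77 |
| 0.5 | 1.00 | 0.75 | 0.75 | 67 | 67 |
| 0.7 | 0.60 | 0.51 | 0.85 | 98 | 59 |
| 0.8 | 0.40 | 0.36 | 0.90 | 139 | 56 |

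The variance cut is therefore 9% to 64% against post values, and 35% to 10% against change, as r goes from 0.3 to 0.8. A simulation of 4,000 trials at each of r = 0.5 and r = 0.7 gave ANCOVA ratios of 0.74 and 0.49, in line with the formula.

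**Step 2. What this means for power (illustration)**

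The standard error on post values is 8 × √(2/50) = 1.6 points. Power is approximately Φ(3/SE − 1.96).
- Post values: 3/1.6 − 1.96 = −0.085, power 0.47.
- Change: SE = 1.6 × √[2(1 − r)]. Power is 0.35, 0.47, 0.68 and 0.84 at r = 0.3, 0.5, 0.7 and 0.8.
- ANCOVA: SE = 1.6 × √(1 − r²). Power is 0.50, 0.58, 0.75 and 0.88 at the same r.

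**Step 3. When baseline means differ**

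Let D be the difference in mean baseline between two groups. With equal SDs, the post-value difference equals the ANCOVA difference plus rD, and the change-score difference equals the ANCOVA difference minus (1 − r)D. Over r = 0.3 to 0.8 a raw post-value comparison thus carries 0.3 to 0.8 of the baseline difference. ANCOVA and change score disagree by 0.7 to 0.2 of it.

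Precision also suffers. With d the baseline difference in SD units, the ANCOVA variance is multiplied by 1 + (d²/98)/(2/50) = 1 + 0.255d². For an assumed d = 0.5 the factor is 1.064. The ratio at r = 0.3 then rises from 0.91 to 0.97, and at r = 0.8 from 0.36 to 0.38.

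**The case against.** **No contrast on LVEF is listed.** The analysis section speaks of subgroups without defining them, and the secondary outcome is an association between biomarkers and CMR findings. Ejection dysfunction could even be binary, in which case a linear model would not apply. This stands as a limit on scope. Still, the article builds three procedure groups, its abstract discussion and Background aim at injury after PCI and after CABG with or without bypass, and it provides an unpaired test. Comparing the procedures is the natural reading.

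**The inputs are assumed.** SD, difference and r are not in the article. The large gains also depend on post values being tested, which it does not state. Against change scores the gain at high r is small: power 0.84 versus 0.88 at r = 0.8. This stands, and is why a range is given for both readings.

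**The precision formula suits randomised groups.** It is only approximate here, as step 3 shows, and one baseline covariate does not deal with other confounding. This also stands. Yet either baseline-using analysis is preferable to a raw post-value test, which carries the starting difference as well.

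**The article is condensed and no SAP is shown.** A fuller plan may contain the model. But the article does state its method for continuous variables, so the point concerns a stated choice.

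A reader might infer three stronger points, none of which the article supports:
- *That scar extent suffers the same loss.* The aim is to "prospectively examine the incidence and extent of new DE-CMR-defined irreversible injury", and "Preintervention and postintervention scans will be read side by side in both surgical techniques". Scar is thus already judged against the first scan. If new scar is unrelated to old scar (r = 0), 1 − r² = 1 and adjustment gains nothing.
- *That LV volumes are affected.* They are not a named outcome.
- *That group differences will be claimed from paired p-values.* The article names an unpaired test for between-group comparison and nowhere says this.

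**Conclusion.** The point holds for LVEF analysed as a continuous measure, and for any other continuous CMR measure not already expressed as new injury. For these, the named tests make no use of the pre-procedure value as a covariate. If post values are compared, the result is less precise than it could be and takes in any baseline difference between groups formed by eligibility. If changes are compared, some precision is still lost.

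The size is a 9% to 64% lower variance against post values, or 35% to 10% against change scores, for r from 0.3 to 0.8 with similar baseline means. It is smaller under imbalance. The true r is unknown and may be modest because preserved LVEF is required.

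This is a moderate, easily remedied efficiency point on secondary or descriptive comparisons. The t tests are not invalid as tests of the means they compare. The primary outcome, 5-year death, is untouched.

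**What to change.** In the Statistical analysis section, state that procedure groups will be compared on LVEF with a linear model of the post-procedure value on procedure group and pre-procedure value, reporting the adjusted between-group difference with its 95% CI. Give the between-group comparison of change scores as a sensitivity analysis. Say that paired tests serve only as within-group description.

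The cost is a sentence or two and no new data, since both scans are already planned; Trial status reports that enrolment had not begun at submission. The downside should be stated alongside: neither analysis removes other confounding between the procedure groups, and the two can give different answers if baselines differ. Any such disagreement should be reported.
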